## Abstract

**Introduction:**

Non-contrast computed tomography (CT) and CT angiography are the gold standard in neuroimaging diagnostics in the case of suspected stroke. CT perfusion (CTP) may play an important role in the diagnosis of stroke mimics (SM), but currently, it is not a standard part of the stroke diagnostic procedure. The project is a multicentre prospective observational clinical research focused on refining the diagnostics of stroke and stroke mimics (SM) in hospital care.

**Aim:**

This study aimed to evaluate the degree of specificity and sensitivity of multimodal CT (NCCT, CTA, and CTP) in the diagnosis of SM versus stroke.

**Methodology:**

In this study, we will include 3,000 patients consecutively admitted to the comprehensive stroke centres with a diagnosis of suspected stroke. On the basis of clinical parameters and the results of multimodal CT and magnetic resonance imaging (MRI), the diagnosis of stroke and SM will be established. To clarify the significance of the use of the multimodal CT scan, the analysis will include a comparison of the blinded results for each imaging scan performed by radiologists and AI technology and a comparison of the initial and final diagnosis of the enrolled patients. Based on our results, we will compare the economic indicators and costs that would be saved by not providing inadequate treatment to patients with SM.

**Conclusion:**

The expected outcome is to present an optimised diagnostic procedure that results in a faster and more accurate diagnosis, thereby eliminating the risk of inadequate treatment in patients with SM.

**Clinical trial registration:**

clinicaltrials.gov, NCT06045455.

## Introduction

Stroke mimics (SM) present a wide variety of neurological disorders that exhibit symptoms similar to those of a proven cerebrovascular accident (CVA—stroke), despite not being a true stroke. Every year, stroke affects approximately 28,000 people across the entire age spectrum in the Czech Republic, out of which one-third of patients succumb to the damage, some patients remain with a permanent deficit, and only a proportion of these patients recover fully from this disease. To achieve a positive outcome for patients with stroke, it is essential to initiate treatment early, which requires the early recognition of symptoms and the diagnosis of stroke. However, a rapid assessment can lead to the unintentional treatment of patients with SM, which is not indicated, is costly, and can lead to complications. A meta-analysis of data from 62,664 patients indicates that the average prevalence of SM is 24.8% (with an interval of 20–50%). The frequency of SM varies and depends on where the diagnosis is conducted and whether the patients are assessed by a physician at the emergency department or by a neurologist (1, 2).

SM can be divided into two main categories: medical SM and functional SM. Medical SM consist of brain disorders (migraine, seizures, posterior reversible encephalopathy syndrome/PRES, epidural/subdural haematomas, hypertensive encephalopathy, or brain tumours) and systemic diseases (electrolyte dysfunction and metabolic/toxic disorders). The frequency of the individual types of SM varies across different studies. The most recent comprehensive review showed the following frequencies of the different types of SM: peripheral vestibular syndrome 23.2%, toxic/metabolic disorders 13.2%, seizures 13%, migraine 7.8%, syncope 6%, mononeuropathy 5%, space-occupying brain lesions 4%, acute confusion 1.9%, dementia 1.2%, and spinal cord lesions 0.7% (3).

CT perfusion (CTP) identifies the ischaemic brain tissue in patients with suspected stroke even when non-contrast head computed tomography (NCCT) is normal (4, 5). CTP can estimate brain regions with a high probability of irreversible infarction (ischaemic core) and areas at risk of infarction (penumbra). CTP is a functional examination of the brain tissue that characterises the state of brain perfusion and provides information on the current functional state of the microcirculation (6). These facts provide very important prognostic information in the cases of successful and unsuccessful acute recanalisation treatment. CTP allows the selection of suitable candidates for recanalisation treatment after 6 h in the case of mechanical thrombectomy (MT) and after 4.5 h in the case of intravenous thrombolysis (IVT), or if the time of stroke onset is unknown. Recent studies have demonstrated the benefit of MT within 6 h from the onset of stroke in patients with a large ischaemic core. The importance of CTP as an indication for acute recanalisation treatment has decreased, but the prognostic and diagnostic roles of CTP is still essential (7). Perfusion imaging abnormalities have also been reported to be useful in differentiating SM from acute ischaemic stroke and may inform treatment decision-making (8–11).

Exclusion of ischaemic stroke and early detection of SM are crucial in reducing the number of unindicated intravenous thrombolysis (IVT) treatments, which is the first choice of treatment for patients with stroke. In the randomised Norwegian Tenecteplase Stroke Trial (NOR-TEST) study that assessed the effect of tenecteplase in ischaemic strokes, IVT was administered to 18% of patients (tenecteplase vs. alteplase) with a diagnosis other than ischaemic stroke (12). Unindicated administration of IVT can cause possible negative implications for patients (extra or intracerebral haemorrhage, orolingual angioedema, etc.), thereby leading to permanent health and social stigma.

The existing literature predominantly consists of a small quantity of case series concerning SM and have often included only patients with seizures or migraines. In reality, the spectrum of SM is much wider. In this respect, the present project is unique when compared with the current published studies.

## Overall goals of the project

This project aims to optimise hospital diagnostics for stroke and SM symptoms, focusing on the specificity and sensitivity of multimodal brain imaging compared to conventional imaging. The specific goals of the study include evaluating diagnostic outcomes between blinded radiologists/AI technology and clinical diagnosis as well as comparing economic indicators to identify potential savings from avoiding unnecessary treatments.

## Methods

The study employs a prospective multicentre observational design in two Czech comprehensive stroke centres, enrolling an estimated 3,000 patients over 3 years.

The inclusion criteria include acute neurological deficits with symptoms lasting up to 24 h and NIHSS ≥0 points (National Institutes of Health Stroke Scale) at enrolment.

The exclusion criteria include age < 18 years, previous severe neurological handicap (mRS = 5), contraindications for CT contrast scan or MRI (pregnancy, severe renal failure, allergy to contrast material, or claustrophobia), and patient non-consent. For the trial flow, see the STARD diagram (Figure 1).

**Figure 1 fig1:**
[figure not shown]
STARD diagram.

### Monitored parameters

The following data will be collected and evaluated in Table 1.

**Table 1 tab1:** Following data will be collected and evaluated.

Patient history	
Age Sex Comorbidities Long-term medication	Hypertension, diabetes mellitus, heart disease, arrhythmia, hyperlipidemia, mental disorders, cephalgia, migraine, epilepsy, oncological disease, cognitive deficit antithrombotic medication, hormonal anticonception
Hospitalisation data	
Date and time of stroke/stroke mimics Date of hospital admission Hospitalisation, duration	standard, ICU
Systolic/diastolic blood pressure Laboratory parameters-INR, glycemia, Increase in liver tests, kidney failure, drugs in the blood	
Clinical data	
mRS NIHSS Neurological deficit Type of treatment Multimodal brain CT scan on admission Follow-up NCCT Brain MRI results Final diagnosis	Pre-morbid, at discharge on admission, 24 h after the admission to hospital NCCT, CTA, CTP during 24–36 h after the admission in indicated patients stroke, stroke mimics
Follow-up visit	
mRS value Recurrence of symptoms Clinical condition	

### Stroke protocol

#### Multimodal CT

All patients with acute neurological deficits (stroke, transient ischaemic stroke (TIA), or SM) will undergo neuroimaging diagnostic procedures as per the stroke protocol, i.e., initial multimodal brain CT (NCCT, CTP, and computed tomography angiography (CTA)), followed by follow-up NCCT within 24–36 h.

The basic CTP parameters define perfusion maps, which express the mean transit time, cerebral blood flow, and cerebral blood volume. Currently, the maps defining the so-called maximum time (Tmax) are also essential. The AI software package allows us to determine the extent of irreversible ischaemia (decrease in CBF below 30% of the reference bilateral value) and potentially the tissue that can be rescued, i.e., penumbra (prolongation of Tmax over 6 s).

Type of CT device—CT Force Siemens.

Stroke protocol: Unenhanced brain: 120 kV (CarekV), 300 mAs (CareDose), collimation 128 × 0.6 mm rotation time 0.5 s Recon: slice 0.75 mm, 5 mm, kernel Hr 40.

CTP: 70 kV, 200 mAs, collimation 48×1.2 mm, brain coverage-4D range: 114 mm.

Cycle time 1.5 s exam time 45 s rotation time 0.25 s contrast medium—40 mL intravenous.

CTA: 120 kV (CarekV), 84 mAs (Care Dose), collimation 128 × 0.6 mm.

Recon: slice 0.5 mm, 3 mm, kernel Hr 36, contrast medium—50 mL intravenous.

#### MRI examination

All patients without a confirmed concordant hypoperfusion or cerebral ischaemia on their previous CT scans will undergo an MRI examination between the third and seventh day after admission to hospital to confirm the diagnosis of SM.

The MRI examination will be performed using the Siemens Prisma, 3.0 T scanner (Siemens, Erlangen, Germany). The imaging protocol includes:localisers;diffusion weighted imaging (DWI) with b-factor values 0, 400, and 800 s/mm2, calculated b-value of 1,000 s/mm2. ST 3.0 mm, GAP 0.6 mm, TR 2900 ms, TE 60 ms, FOV 256 mm, BW 868 Hz/Px, number of slices 40, TA 2:09;reconstructed maps of an apparent diffusion coefficient (ADC maps);3D FLAIR sequence. The examination will be performed in the sagittal plane with 1 mm MPR axial and coronal reconstructions. TR 5500 ms, TE 383 ms, ST 1 mm, number of slices 160, GAP 0, TI 1800 ms, FA T2 Var. deg., BW 751 Hz/Px, TF 220, TA—acquisition time 3:46. Total examination time 6:12+ shimming time.

Follow-up brain MRI will be performed on the following patients as per the stroke protocol:Patients with a negative initial multimodal CT scan.Patients with discordant CTP results, which means that the location of the hypoperfusion does not correspond with the neurological symptoms, or patients with CTP technical artefacts.Patients with a negative follow-up brain NCCT.Patients with an NIHSS score of zero upon admission to the hospital and 24 h after the onset of TIA.

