### Analyse of CT and MRI examination

The results of NCCT, CTA, and CTP will be evaluated by a blinded radiologist against the clinical diagnosis and will then be compared with the multimodal CT examination evaluated by AI. The concordance of a positive CTP finding in relation to the clinic will be assessed by a specialist stroke neurologist. The AI software (e-Stroke, Brainomix, Oxford) provides a fully automated scoring tool for analysing CT and MRI examinations. The software calculates e-ASPECT and the volume of ischaemia; it analyses CTP and the values of collateral circulation. Furthermore, it can determine the area of vascular occlusion and the size of ischaemia on MRI. In this respect, Brainomix e-STROKE software is a unique and irreplaceable tool.

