### Determination of the definitive diagnosis

Two neurologists specialised in treating and diagnosing stroke will confirm the diagnosis independently.

The following patients will be diagnosed with an ischaemic stroke:Patients with a finding of hypodensity corresponding with subacute ischaemia on the initial brain CT examination.Patients with a new subacute ischaemic lesion on the follow-up NCCT scan within 36 h from the onset of the neurological deficit.Patients with an ischaemic brain lesion on their MRI scan within 3–7 days from the onset of the neurological deficit.

The diagnosis of SM will be determined by the following parameters:organic lesion of aetiology other than ischaemic stroke on the NCCT scan,negative CTP, discordant CTP, and negative control brain MRI,two neurologists and two radiologists specialised in treating and diagnosing stroke will confirm the diagnosis of SM independently, considering the correlation of imaging and clinical data (see clinical data checklist). The radiologists will also assess other thresholds during the CTP examination than the classically established ones (e.g., T max less than 6 s). Both stroke consultants will assess the final diagnosis for the whole group with and without knowledge of the CTP result.

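### The MRI that helps decide stroke versus mimic is ordered partly because of the CTP result and aimed at confirming SM, and no stated mask covers its reading

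*Protocol article*

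**What the plan says.** All places are in the Protocol article.

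*MRI examination.* The opening sentence takes "All patients without a confirmed concordant hypoperfusion or cerebral ischaemia on their previous CT scans" and says that they "will undergo an MRI examination between the third and seventh day after admission to hospital to confirm the diagnosis of SM". The section then lists four groups for follow-up MRI:

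- a negative initial multimodal CT;
- "Patients with discordant CTP results, which means that the location of the hypoperfusion does not correspond with the neurological symptoms", or CTP artefacts;
- "Patients with a negative follow-up brain NCCT";
- an NIHSS of zero both on admission and at 24 hours.

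*Analyse of CT and MRI examination.* The mask is stated as follows: "The results of NCCT, CTA, and CTP will be evaluated by a blinded radiologist against the clinical diagnosis". MRI is not named in that sentence. Of the AI software, the section says that "it can determine the area of vascular occlusion and the size of ischaemia on MRI".

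*Determination of the definitive diagnosis.* Ischaemic stroke can be established by hypodensity on the initial CT, by a new lesion on follow-up NCCT, or by a lesion on MRI. The SM criteria put negative or discordant CTP beside a negative MRI. Two neurologists and two radiologists confirm SM, relating the images to the clinical data. The radiologists also examine CTP thresholds other than the usual ones. The section ends: "Both stroke consultants will assess the final diagnosis for the whole group with and without knowledge of the CTP result".

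**The concern.** In an accuracy study the reference standard should be reached without knowledge of the index test. Here the index test helps decide who has the reference MRI, and the request is framed as confirming one of the two possible answers. The radiologists who confirm the mimics also work on the CTP images. Nothing stated keeps the CTP or AI result from whoever reads the MRI or the follow-up NCCT.

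A reader who knows that CTP was negative, and that the scan is meant to confirm a mimic, may more readily dismiss a small diffusion lesion. Each lesion so dismissed turns a CTP miss into a correct SM call. That removes a false negative and adds a true negative, so sensitivity and specificity of CTP both rise. The consultants' assessment without CTP would inherit the error, because it uses the same reading. Enrolling more patients narrows the confidence interval but does not reduce this bias.

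**Working it through.** **1. Who is masked to what, as stated**

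| Assessment | Stated mask |
|---|---|
| Admission NCCT, CTA, CTP (radiologist) | To the clinical diagnosis |
| Consultants' final diagnosis | Made twice, once without CTP |
| Follow-up NCCT and MRI reading | None stated to CTP or AI |
| Radiologists' confirmation of SM | None stated; the radiologists also assess CTP thresholds |

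The article also does not say which of the consultants' two diagnoses is the reference standard.

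**2. How far MRI depends on CTP**

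The opening sentence makes CTP part of the rule. In the list, the first two groups depend on CTP and the last two do not. The two rules disagree for a patient with concordant hypoperfusion and a negative follow-up NCCT: no MRI under the opening sentence, MRI under the list. This bears on masking, because under the opening sentence the mere existence of an MRI can reveal the CTP result.

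**3. Illustration of size**

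The plan gives no figure to reproduce on this point.

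From the document: N = 3,000 planned; SM share 34% (pilot, 37/109). Strokes = 3,000 × 0.66 = 1,980; mimics = 1,020.

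Assumed, without a source in the document: true CTP sensitivity for stroke 70% or 80%; specificity 90% or 95%; share *r* of CTP-negative strokes relabelled SM of 5%, 10% or 20%.

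Apparent sensitivity = TP / [TP + FN × (1 − r)]

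Half-width = 1.96 × √[Se(1 − Se)/1,980]

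At 80%: TP = 1,584, FN = 396, half-width 1.76 points.
- r = 5%: 1,584/1,960.2 = 80.8% (+0.8)
- r = 10%: 1,584/1,940.4 = 81.6% (+1.6)
- r = 20%: 1,584/1,900.8 = 83.3% (+3.3)

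At 70%: TP = 1,386, FN = 594, half-width 2.02 points.
- r = 5%: 1,386/1,950.3 = 71.1% (+1.1)
- r = 10%: 1,386/1,920.6 = 72.2% (+2.2)
- r = 20%: 1,386/1,861.2 = 74.5% (+4.5)

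The shift stays below the half-width at r = 5% in both cases and at r = 10% with 80% sensitivity. It exceeds it at r = 10% with 70% sensitivity and at r = 20% in both.

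Apparent specificity = (TN + r × FN) / (TN + r × FN + FP). The largest change in the grid is at 70% sensitivity, 90% specificity and r = 20%: (918 + 118.8)/(918 + 118.8 + 102) = 91.0%, a rise of 1.0 point. The smallest is about 0.1 point.

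**The case against.** The strongest reply is that this is a condensed article. Reading procedures are often left to a full protocol that is not shown, and the abstract does promise blinded results for each scan. Silence on an MRI mask would be weak evidence by itself. But the abstract does not say what the reader is blinded to, and the article does set out masking in two places, neither of which reaches the MRI reading. The firmer ground is what the article states: the one-directional purpose, the partly CTP-dependent trigger, CTP within the SM criteria, and confirming radiologists who also handle CTP.

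There are real safeguards. An MRI lesion establishes stroke whatever CTP showed, SM needs independent confirmation by four specialists, and the consultants make one assessment without CTP. These limit the problem. They do not remove it, because they rely on an image reading that is not stated to be masked.

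A reader might infer more than the document supports:

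- *That MRI is ordered only because of CTP.* Two of the four listed groups do not depend on it.
- *That the referral discloses CTP, or that the MRI report is written with CTP known.* Neither is described. The text permits it and does not say it happens.
- *That AI-scored MRI enters the final diagnosis.* The article describes a capability of the software; no AI output is among the diagnostic criteria.
- *That MRI alone decides every CTP-negative stroke.* Initial or follow-up NCCT can also establish stroke, so fewer than the 396 or 594 above may hinge on MRI. The illustration also treats CTP alone, whereas the aim is multimodal CT: a CTP-negative stroke visible on the admission NCCT is not a multimodal miss.

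**Conclusion.** The point holds as a risk of review bias. Followed as written, the plan allows the MRI and follow-up NCCT that help settle the diagnosis to be read with CTP known, and it frames the MRI as confirming SM. The likely direction favours CTP. The bias is not demonstrated, and its size cannot be derived from the document.

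Under the stated assumptions, apparent sensitivity rises by 0.8 to 4.5 points and specificity by about 0.1 to 1.0 point. A reader might conclude that the bias always matches or exceeds the statistical error. It does not: it is below the half-width of 1.8 to 2.0 points at the low end of the range and above it only towards the high end. The change is worth making because it is cheap and because a reading made with CTP known can be replaced only by a fresh masked reread.

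**What to change.** 1. In *MRI examination*, give the scan a neutral purpose, for example to establish the final diagnosis, in place of "to confirm the diagnosis of SM".
2. In *Analyse of CT and MRI examination*, state that MRI and follow-up NCCT are read for acute ischaemia by an existing study radiologist without that patient's CTP, CTA or AI output. Lock the read before adjudication and before any work on CTP thresholds.
3. State that AI-scored MRI does not enter the final diagnosis.
4. In *Determination of the definitive diagnosis*, name the consultants' CTP-free diagnosis, based on that masked read, as the reference standard for CTP accuracy.
5. Reconcile the opening sentence of *MRI examination* with its list of four groups, so that one rule says who has an MRI.

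Cost: protocol wording, plus some logistics in allocating and sequencing reads between the existing radiologists. The sequencing needs care, because the radiologists who confirm SM also assess CTP thresholds and the article does not say whether either of them reads the admission CT. The masking itself needs no additional scan.

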### Analyse of CT and MRI examination

The results of NCCT, CTA, and CTP will be evaluated by a blinded radiologist against the clinical diagnosis and will then be compared with the multimodal CT examination evaluated by AI. The concordance of a positive CTP finding in relation to the clinic will be assessed by a specialist stroke neurologist. The AI software (e-Stroke, Brainomix, Oxford) provides a fully automated scoring tool for analysing CT and MRI examinations. The software calculates e-ASPECT and the volume of ischaemia; it analyses CTP and the values of collateral circulation. Furthermore, it can determine the area of vascular occlusion and the size of ischaemia on MRI. In this respect, Brainomix e-STROKE software is a unique and irreplaceable tool.

### Determination of the definitive diagnosis

Two neurologists specialised in treating and diagnosing stroke will confirm the diagnosis independently.

The following patients will be diagnosed with an ischaemic stroke:Patients with a finding of hypodensity corresponding with subacute ischaemia on the initial brain CT examination.Patients with a new subacute ischaemic lesion on the follow-up NCCT scan within 36 h from the onset of the neurological deficit.Patients with an ischaemic brain lesion on their MRI scan within 3–7 days from the onset of the neurological deficit.

The diagnosis of SM will be determined by the following parameters:organic lesion of aetiology other than ischaemic stroke on the NCCT scan,negative CTP, discordant CTP, and negative control brain MRI,two neurologists and two radiologists specialised in treating and diagnosing stroke will confirm the diagnosis of SM independently, considering the correlation of imaging and clinical data (see clinical data checklist). The radiologists will also assess other thresholds during the CTP examination than the classically established ones (e.g., T max less than 6 s). Both stroke consultants will assess the final diagnosis for the whole group with and without knowledge of the CTP result.

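### Hypodensity on the admission CT is by itself enough for the reference diagnosis of ischaemic stroke, so the reported specificity of NCCT is biased upward by an amount the documents do not determine

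*Protocol article*

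**What the plan says.** The aim in the protocol article's Abstract is to "evaluate the degree of specificity and sensitivity of multimodal CT" in separating stroke mimics (SM) from stroke. Under Multimodal CT, every patient has "initial multimodal brain CT (NCCT, CTP, and computed tomography angiography (CTA)), followed by follow-up NCCT within 24–36 h". The Discussion sets NCCT plus CTA plus CTP against NCCT alone and against NCCT plus CTA. The admission NCCT is therefore both a component of the index test and a strategy in its own right.

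Determination of the definitive diagnosis opens its stroke list with "The following patients will be diagnosed with an ischaemic stroke" and gives three alternatives. The first is "Patients with a finding of hypodensity corresponding with subacute ischaemia on the initial brain CT examination". The other two are a new subacute lesion on the follow-up NCCT and an ischaemic lesion on MRI. The first asks for no later confirmation.

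The same section provides two checks: "Two neurologists specialised in treating and diagnosing stroke will confirm the diagnosis independently", and "Both stroke consultants will assess the final diagnosis for the whole group with and without knowledge of the CTP result". Under Analyse of CT and MRI examination, "The results of NCCT, CTA, and CTP will be evaluated by a blinded radiologist against the clinical diagnosis", followed by a comparison with the AI reading.

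**The concern.** When a positive index test is sufficient for the reference diagnosis, the reference cannot fully expose that test's errors. A mimic whose admission NCCT is taken to show subacute ischaemia meets the first stroke criterion. If that stands, the patient moves from false positive to true positive, and the mimic denominator shrinks as well. This is incorporation bias. The with-and-without assessment addresses it for CTP, but nothing equivalent is stated for NCCT.

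There are two consequences. First, the levels of sensitivity, specificity and predictive values, which the Statistic analysis section says will be reported with confidence intervals, are off in a known direction. Enrolling 3,000 patients narrows the interval without moving the estimate towards the truth. Second, the rule works against CTP. A mimic with a false hypodensity and a correctly negative CTP is labelled stroke, so CTP is charged with a false negative in exactly the patient where it corrected NCCT.

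**Working it through.** **Plan figures.** The pilot's SM share is 37/109 = 33.9%, matching the stated 34%. The stated minimum of 718 follows from 16 × 0.34 × 0.66 / 0.10² = 359.04, or 359 per group and 718 in total; it has no bearing on this point. The article states no NCCT specificity or false-positive rate, so there is no plan figure to reproduce and the size can only be given as a range.

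**Inputs.** From the article: N = 3,000 and 34% mimics, giving 1,020 mimics and 1,980 strokes (Statistic analysis, Pilot project); NCCT sensitivity 33% (Discussion), giving 0.33 × 1,980 = 653.4 true positives. Assumed: true NCCT specificity of 98%, 95% or 90%; a CTP false-positive rate of 10%, independent of NCCT; a share *r* of false hypodensities that the adjudicators reject. Stroke is taken as the positive state.

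**Specificity of NCCT.** False hypodensities F = (1 − specificity) × 1,020. Those accepted, (1 − r)F, leave the mimic group.
Reported specificity = 1 − rF / [1,020 − (1 − r)F].

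| True specificity | F | r = 0 | r = 0.5 | r = 1 |
|---|---|---|---|---|
| 98% | 20.4 | 100% | 1 − 10.2/1,009.8 = 99.0% | 98% |
| 95% | 51 | 100% | 1 − 25.5/994.5 = 97.4% | 95% |
| 90% | 102 | 100% | 1 − 51/969 = 94.7% | 90% |

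**PPV of NCCT for stroke.** True value = 653.4/(653.4 + F) = 97.0%, 92.8%, 86.5%. Reported value = [653.4 + (1 − r)F]/(653.4 + F): 100% in each case at r = 0, and 98.5%, 96.4%, 93.2% at r = 0.5.

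**Sensitivity of NCCT at r = 0.** (653.4 + F)/(1,980 + F) = 33.7%, 34.7%, 36.3% against 33%.

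**Combinations of NCCT and CTP.** The article does not state the combination rule, so two are shown.
- *Positive if either is positive.* True specificity = 0.9 × NCCT specificity = 88.2%, 85.5%, 81.0%. Reported: 90.0% throughout at r = 0; 89.1%, 87.7%, 85.3% at r = 0.5. The gap to NCCT alone is truly 9.8, 9.5 or 9.0 points and is reported as 10.0 at r = 0, so this contrast moves by at most 1 point.
- *CTP decides.* The combination stays at 90% with or without the bias. The gap to NCCT alone is truly 8, 5 or 0 points and is reported as 10 at r = 0, a distortion of 2, 5 or 10 points against CTP.

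**False negatives charged to CTP at r = 0.** 0.9 × F = 18, 46 or 92 patients.

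**If SM is the positive state.** The NCCT specificity figures become sensitivity for SM, with unchanged values.

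**The case against.** The strongest reply is that the rule is not mechanical. The index scans are read by a blinded radiologist and by AI, while two neurologists confirm the diagnosis. A hypodensity reported in the index reading but not accepted by the neurologists remains a false positive. A reader might infer that NCCT cannot have a false positive and that its specificity is 100% by definition. The article does not support this: it would require the index and reference readings to coincide, and nowhere are they said to.

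A reader might also infer that these patients escape MRI. The general rule under MRI examination does direct MRI to patients without ischaemia or concordant hypoperfusion on CT. However, the list that follows adds patients with a negative follow-up NCCT, discordant CTP or CTP artefacts. A spurious hypodensity that is gone at 24–36 h leads to MRI. Such a patient with negative or discordant CTP and a negative MRI then meets the first stroke criterion and also fits the SM parameters, for which two neurologists and two radiologists weigh imaging against the clinical data. The checklist they use is not shown and may guide them.

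Third, inflation in every combination containing NCCT does not follow. It carries over under an any-positive rule but not where CTP decides, and the rule is unstated. Nor is it fixed whether stroke or SM is the positive state.

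These points limit the size of the bias; they do not remove it. The first criterion is categorical, nothing says the neurologists may set it aside, and no text gives negative follow-up NCCT or MRI precedence over it. Any share of false hypodensities accepted below 100% still biases specificity upward unless that share is zero.

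**Conclusion.** The point holds as a directional bias. An index-test finding is sufficient for the reference diagnosis, the stated safeguard covers CTP only, and precedence of contrary follow-up imaging is unspecified. NCCT specificity and PPV for stroke (or sensitivity for SM) are biased upward towards 100%, as is the specificity of any-positive combinations.

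For NCCT specificity the overstatement runs from zero, if every false hypodensity is overruled, to 2, 5 or 10 points, if all are accepted, at assumed true specificities of 98%, 95% and 90%. If half are rejected it is about 1.0, 2.4 and 4.7 points. These rates are assumptions. The PPV figures also apply a sensitivity quoted for ischaemic stroke to all 1,980 strokes.

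The reported mimic share would fall from 34% to 33.3%, 32.3% or 30.6% if all are accepted ((1,020 − F)/3,000). A reader might infer that the cost results shift with it. The article bases costs on the average cost of thrombolysis and does not state that link, so it is not claimed here.

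**What to change.** For the primary accuracy analysis, do not let the admission CT finding suffice. Classify such a patient as ischaemic stroke only when the follow-up NCCT already planned for all patients ("followed by follow-up NCCT within 24–36 h"), or an MRI, shows an acute or subacute infarct, not a chronic one, that matches the deficit. That reading should be made without the admission CT report.

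Reword *new* in the second stroke criterion so that an acute or subacute infarct persisting from admission qualifies and an old one does not. Simply deleting the word would let chronic infarcts in.

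State that negative follow-up imaging takes precedence over the first criterion. Report the present rule as a sensitivity analysis, so that the effect of the change is visible.

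This alters only the classification used for analysis, with a rewording and a reader instruction; no scan is added and patient care is unchanged. The costs are that patients without follow-up imaging need clinical adjudication, that a misreading repeated on the follow-up NCCT survives because the modality is the same, and that reported specificity may be somewhat lower.
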